**Figure 2 F2:**
[figure not shown]
The overall flow of data management.

### Statistical analysis

2.6

Before performing statistical analysis, we shall invite statistical analysts to make plans and specify detailed steps, then carefully examine the data collected. All statistical analysis processes are programmed and archived for future reference.

#### 
Statistical methods

2.6.1

1.Continuous variables conforming to the normal distribution are expressed by standard deviation and mean, and the difference between groups is analyzed by one-way ANOVA.2.If it conforms to non-normal distribution, we use the median, upper quartile (Q1), lower quartile (Q3), 95% confidence interval to express, and rank-sum test (Wilcoxon method) for analysis.3.The classified data are expressed in terms of quantity and percentage and analyzed by the χ^2^ test and Fisher exact probability method.4.If considering the influence of baseline confounding factors, logistic regression analysis is used. The correlation between variables is analyzed by Spearman or Pearson correlation.

We use SPSS version 23.0 (IBM Corporation, Armonk, NY) to conduct all analyses. The general statistical test uses a bilateral test, and bilateral *P* < .05 is considered statistically significant.

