(2)Diagnostic criteria of hypercholesterolemia:According to the Expert Consensus on Diagnosis and Treatment of Dyslipidemia with Integrated Traditional Chinese and Western Medicine,^[12]^ hypercholesterolemia is diagnosed when total cholesterol (TC) ≥ 5.18 mmol/L. Based on the TC level, we divide patients into 3 groups: patients with TC < 5.18 mmol/L belong to normal TC (NTC) group, 5.18 ≤ TC < 6.19 mmol/L is borderline-high TC (BHTC) group, those with TC ≥ 6.19 mmol/L belong to high TC (HTC) group.(3)Diagnostic criteria of HTN:If the patients have been diagnosed with HTN or are currently taking antihypertensive drugs, we will classify they as HTN group.^[13]^ Otherwise, we will redefine HTN as systolic blood pressure (BP) ≥ 130 mm Hg or diastolic BP ≥ 80 mm Hg according to the recently published 2017 ACC/AHA guidelines.^[14]^

#### 
Inclusion criteria

2.2.2

1.Patients aged from 35 to 75 years old, male or female.2.Those who were hospitalized between September 1, 2014, and September 1, 2019.3.Those with CHD angina pectoris and have undergone CAG in the inpatient department of internal cardiovascular medicine.4.The diagnosis of hypercholesterolemia, CHD angina pectoris and HTN is accorded with the diagnostic criteria.

#### 
Exclusion criteria

2.2.3

1.Those with other cardiac diseases, gastroesophageal reflux disease, or hiatal hernia, neurosis, spinal, or vertebral artery cervical spondylosis, hyperthyroidism, climacteric syndrome, etc.2.Those with myocarditis, cardiomyopathy, acute myocardial infarction, third degree of heart failure, severe heart valve disease, major diseases such as malignant tumor and serious metabolic diseases, liver failure, or renal failure.3.Those with psychotic disorders or cognitive dysfunction.4.Those of childbearing age and have fertility requirements, pregnant women, or lactating women.5.Those allergic to the iodine contrast medium.6.Those who are not suitable for the study, as judged by the researcher.

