### Research group

2.3

Based on the TC level, we divide patients into 3 groups, and the correlation between the TC and the degree of CAS is evaluated. With or without HTN will be further stratified to assess the effect of with or without HTN on the correlation between TC levels and the degree of CAS. The 6 subgroups are: NTC/-HTN group, NTC/+HTN group, BHTC/-HTN group, BHTC/+HTN group, HTC/-HTN group, HTC/+HTN group. The NTC/-HTN group is taken as the reference group. The flow diagram is shown in Figure 1.

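### The group comparisons treat ordered classes of measured total cholesterol as unordered, and the hypertension question is built on those classes; analysing TC per mmol/L would be a cheap improvement

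*Protocol article*

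**What the plan says.** Section 2.4 (Observation indicators) lists TC among the biochemical values taken from the first day of hospitalisation. Section 2.2.1 (Diagnostic criteria) then forms three classes: "patients with TC < 5.18 mmol/L belong to normal TC (NTC) group", "5.18 ≤ TC < 6.19 mmol/L is borderline-high TC (BHTC) group", and "those with TC ≥ 6.19 mmol/L belong to high TC (HTC) group".

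Section 2.3 (Research group) builds both aims on these classes. The first is "Based on the TC level, we divide patients into 3 groups, and the correlation between the TC and the degree of CAS is evaluated". The second splits each class by hypertension, giving six subgroups: "The NTC/-HTN group is taken as the reference group".

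Section 2.6.1 (Statistical methods) supplies the tests. For normally distributed continuous variables, "the difference between groups is analyzed by one-way ANOVA"; for the rest, "rank-sum test (Wilcoxon method) for analysis". It also lists logistic regression for when baseline confounders are considered, and adds: "The correlation between variables is analyzed by Spearman or Pearson correlation". It names no trend test or ordered contrast. It does not say whether TC enters the correlation or the regression in mmol/L or as a class.

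**The concern.** The first aim is worded as a graded relation: does stenosis rise with cholesterol? A comparison of three classes with an order-blind test answers a coarser question, in two ways. Every value below 5.18 mmol/L counts as the same, and likewise within each higher class. NTC, BHTC and HTC are also handled as three unrelated labels, so a steady rise across them earns no more credit than any other pattern of differences of the same size.

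The stake is greatest for the hypertension question. Section 2.3 poses it as a stratification of the TC classes, so it inherits the coarse coding and depends on whatever number of patients falls in the top class once that class is split in two. No listed analysis is stated to test whether the TC-stenosis slope differs by hypertension status.

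**Working it through.** The article gives no power, effect size, TC mean, TC SD or class shares, so there is no figure of its own to reproduce. What follows is a sensitivity calculation.

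**Inputs from the article.** Cut points 5.18 and 6.19 mmol/L (2.2.1); 1000 patients (2.1); two-sided alpha 0.05 (2.6.1).

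**Assumed inputs.** TC normal, with mean and SD varied; stenosis linear in TC.

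**Step 1: share of TC variance kept by the classes.** With z₁ = (5.18 − μ)/σ and z₂ = (6.19 − μ)/σ, let p_k be the class probabilities and m_k the class means in SD units. The share kept is R = Σ p_k m_k².

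Example with μ = 4.5, σ = 1.1:
- z₁ = 0.68/1.1 = 0.618 and z₂ = 1.69/1.1 = 1.536.
- p = 0.732, 0.206, 0.062 and m = −0.450, 1.005, 1.970.
- R = 0.148 + 0.208 + 0.241 ≈ 0.60.

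Over means 4.0 to 5.7 and SDs 0.9 to 1.2, the share lost (1 − R) runs from 19% (mean 5.7, SD 0.9) to 66% (mean 4.0, SD 0.9). In that last case only about 7 of 1000 patients would be in HTC. Log-normal TC over the same means and SDs gives losses of about 19% to 53%.

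**Step 2: power.** A 1-df test has 80% power at noncentrality 7.85. If numeric TC reaches that value, the three-class test has noncentrality 7.85 × R on 2 df. A trend test with scores 0, 1, 2 has 7.85 × R_t on 1 df, where R_t is the squared correlation of the score with TC. In the example, 7.85 × 0.598 = 4.69 gives 48% on 2 df, and 7.85 × 0.591 = 4.64 gives 58% on 1 df.

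| TC mean, SD (assumed) | HTC per 1000 | R | R_t | Numeric TC | 2-df group test | 1-df trend |
|---|---|---|---|---|---|---|
| 3.9, 1.0 | 11 | 0.35 | 0.34 | 80% | 30% | 38% |
| 4.2, 1.0 | 23 | 0.47 | 0.46 | 80% | 38% | 47% |
| 4.5, 1.1 | 62 | 0.60 | 0.59 | 80% | 48% | 58% |
| 5.0, 1.1 | 140 | 0.73 | 0.72 | 80% | 56% | 66% |

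The first row's mean is set so that 9.9% of patients exceed 5.18 mmol/L. That is the only hypercholesterolemia share in the article (Discussion), and it describes screened hypertensive people, not this cohort.

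**Step 3: dependence on effect size.** With N = 1000 and the noncentral F distribution, a TC-stenosis correlation of 0.10 gives 88.8% power on numeric TC and 37%, 47%, 58% and 68% on the group test in the four rows. At a correlation of 0.15 the figures are 99.8% against 71%, 84%, 92% and 96%. The gap narrows as the effect grows.

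**Step 4: what each remedy recovers.** R_t is almost equal to R, so a trend test recovers the cost of the second degree of freedom: 80% power needs noncentrality 9.63 on 2 df against 7.85 on 1 df, and 9.63/7.85 = 1.23, about 23% more patients. It does not recover what the classes discard. Only numeric TC does that.

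**The case against.** The strongest reply is that the first objective already has a suitable method. Section 2.3 speaks of correlation, section 2.6.1 lists Spearman or Pearson, and TC is held as a number; the natural reading is TC in mmol/L against Gensini score. This stands, and it limits the point. A reader might infer that the study as a whole throws away much of its cholesterol information, or that the correlation is the only listed method able to use numeric TC. The article supports neither: the correlation can keep scale and order, and logistic regression could take numeric TC with adjustment. What remains is that the correlation names no variables, is unadjusted, yields no effect per mmol/L and does not test whether hypertension changes the relation, and that the article does not say TC enters the regression as a number.

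Second, the classes come from a cited consensus and the objective speaks of hypercholesterolemia, a diagnosis. Comparing diagnostic categories is legitimate, which is a reason to keep them for description. It does not justify ignoring their order.

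Third, the ANOVA sentence is generic and does not name the Gensini score. If that score is non-normal, the rank-sum branch applies, which as named compares two groups. The 2-df power figures therefore belong to the ANOVA branch. The rank-sum branch, whether used pairwise or extended to three groups, is equally blind to order.

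Fourth, trend contrasts and splines are often left to an analysis plan. That would answer a complaint about missing detail. Here the article states the class coding and the tests, and the point concerns that choice.

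**Conclusion.** The point holds for the group comparisons and the hypertension question, and not for the TC-stenosis analysis as a whole. The plan treats ordered classes of a measured variable as unordered and bases the subgroup question on them.

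The size is conditional. It is tempting to state the loss of a quarter to two thirds of the TC information as a fact about this study, but that depends on a TC distribution the article does not give and on a linear relation. Over the assumptions tried, the loss is about 19% to 66% of the TC variance, with the upper end only in an extreme case. Where numeric TC has 80% power, the 2-df test has about 30% to 56% and a trend test about 38% to 66%; for stronger effects the difference is smaller. This is a cheap improvement, not a fault that invalidates the plan.

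**What to change.** In sections 2.3 and 2.6.1:

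- Make TC in mmol/L the exposure for inference, reporting the effect on Gensini score per 1 mmol/L from the adjusted model, with a spline in TC as a check of shape.
- Answer the hypertension question with a TC-by-hypertension interaction in that model.
- Keep NTC, BHTC, HTC and the six subgroups for clinical description.
- Where the TC groups are tested, use a 1-df trend test across the ordered classes.

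The cost is analysis wording only: no new data are needed, and section 2.6 already foresees that analysts will set out detailed steps before the analysis. The downside is that a single linear term is less sensitive to a pure threshold effect; the spline and the retained group description cover that.

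### The rule for skewed variables names a two-sample test (Wilcoxon rank-sum), but the design compares 3 cholesterol groups and 6 cholesterol/hypertension subgroups

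*Protocol article*

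**What the plan says.** Section 2.3 (Research group) of the protocol article defines the comparisons. For the main grouping: "Based on the TC level, we divide patients into 3 groups, and the correlation between the TC and the degree of CAS is evaluated". For the second layer: "The 6 subgroups are: NTC/-HTN group, NTC/+HTN group, BHTC/-HTN group, BHTC/+HTN group, HTC/-HTN group, HTC/+HTN group". It then fixes a comparator: "The NTC/-HTN group is taken as the reference group".

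Section 2.6.1 (Statistical methods) chooses the test by type of variable, not by outcome:

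- Item 1, normal continuous variables: "the difference between groups is analyzed by one-way ANOVA".
- Item 2, non-normal continuous variables: "rank-sum test (Wilcoxon method) for analysis".
- Item 3, categorical variables: chi-square and Fisher exact tests.
- Item 4: logistic regression where baseline confounding is considered, and Spearman or Pearson correlation between variables.

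The section closes with a single threshold: "The general statistical test uses a bilateral test, and bilateral *P* < .05 is considered statistically significant". It names no rank test for more than two groups.

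**The concern.** Items 1 and 2 answer the same question, whether a continuous variable differs between groups, for two kinds of distribution. Item 1 names a test for any number of groups. Item 2 names a test for exactly two. With three or six groups, item 2 cannot be carried out as an overall test. Whoever follows it literally must either depart from the text or break the comparison into pairs.

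This matters most for the degree of stenosis. Section 2.4 builds the Gensini score by multiplying stenosis points (1, 2, 4, 8, 16, 32) by site weights from 0.5 to 5 and summing over lesions. If that score is skewed, its comparison across TC groups and subgroups falls under the rule that does not fit. Pairwise testing at a flat .05 would then not hold a 5% error rate for a statement that the score differs between groups.

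**Working it through.** The article gives no familywise error or power figure, so there is none to reproduce. The stated level is 0.05, two-sided.

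**1. Does the named test fit?** The number of groups is 3 or 6 (section 2.3). The rank-sum test handles 2, one-way ANOVA handles any number. Only the normal branch fits the design.

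**2. Is the Gensini score likely to reach item 2?** From section 2.4:

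- A total occlusion of the left main artery contributes 32 × 5 = 160.
- A stenosis of at most 25% in the distal LAD contributes 1 × 1.0 = 1.

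A non-negative sum whose single-lesion terms differ by a factor of 160 is probably right-skewed. This is inferred from the rule; the article gives no distribution for the score.

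**3. What would unadjusted pairwise testing do?** For m independent tests at 0.05, the chance of at least one false positive is 1 − 0.95^m:

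- m = 5 (each other subgroup against NTC/-HTN): 1 − 0.95^5 = 0.226.
- m = 3 (all TC pairs): 1 − 0.95^3 = 0.143.

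Pairwise tests share groups and are not independent, so these values are too high. The rate was therefore simulated under the null with log-normal outcomes and a total of 1000 patients (section 2.1). The article gives no group sizes, so every split is an assumption. In the six-group rows the first cell is NTC/-HTN.

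| Comparisons | Assumed group sizes | Replicates | At least one P < .05 |
|---|---|---|---|
| 5 vs reference | equal | 2000 | 0.173 |
| 5 vs reference | equal (167 or 166 each) | 4000 | 0.171 |
| 5 vs reference | 200/400/80/170/50/100 | 4000 | 0.193 |
| 5 vs reference | 188/562/42/128/20/60 | 2000 | 0.212 |
| 3 TC pairs | 333/333/334 | 4000 | 0.125 |
| 3 TC pairs | 600/250/150 | 4000 | 0.120 |

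Two further 2000-replicate runs for the 3 TC pairs, one balanced and one unbalanced, gave 0.111 and 0.125. The log-normal shape is not critical: without ties, the null distribution of a rank test does not depend on the shape of the outcome.

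**4. Does the replacement hold its level?** In the 4000-replicate runs, Kruskal-Wallis at 0.05 rejected in 0.054 (equal) and 0.047 (unequal) of replicates with three groups, and in 0.042 and 0.049 with six.

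**5. What would adjusted follow-up look like?** With Holm over the five comparisons with NTC/-HTN, the smallest p-value is held to 0.05/5 = 0.01, the next to 0.05/4 = 0.0125, and so on up to 0.05.

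**The case against.** The strongest reply is that the stated aim is a correlation and item 4 supplies it. Spearman correlation of TC with the Gensini score is one test, valid for skewed data, with no pairwise multiplicity. That stands. A reader might infer that the study has no valid test of its main question, and the article does not support this. ANOVA and the chi-square test also cover normal and categorical variables. But Spearman uses TC as a continuous variable. It does not compare the three TC groups or the six subgroups that section 2.3 sets up, and logistic regression needs a categorical outcome.

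A second reply is that the wording may be loose. Kruskal-Wallis is the several-sample test on Wilcoxon rank scores, and its placement opposite one-way ANOVA would suit that reading. This is possible, but the text does not say so. If it was meant, a few words settle it.

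A third reply is that post-hoc procedures and multiplicity corrections are commonly left to a fuller analysis plan, and that section 2.6 promises detailed steps before analysis. This also stands. The missing correction is not itself a fault of a condensed article, and a general .05 threshold does not exclude one. The reply does not rescue item 2, which names a test instead of leaving the choice open.

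Finally, item 2 is a general rule and is not tied to the Gensini score by name. That is why the link is put as probable.

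**Conclusion.** The test named in item 2 does not fit the number of groups in section 2.3. This is an error in stated text, and it should be fixed. It probably affects the group comparison of the Gensini score, on the inference that the score is right-skewed.

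The size is conditional. If the rank-sum test were applied at unadjusted .05 to the five comparisons with NTC/-HTN, the familywise error would be about 17% to 21%, depending on assumed group sizes. Those five have the best support because the article names the reference group, although it attaches no test to it. Testing the three TC pairs would give about 12%, but the text does not state that they will be tested. One could also count all 15 subgroup pairs, for which the simulations gave 34% to 36%. Nothing in the article proposes that analysis, so the figure should not be held against it.

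The stronger conclusion, that the main analysis is invalid and false positives are certain to multiply, does not follow. The defect is one misfitting test name in a retrospective, exploratory study, and it can be corrected before the data are analysed.

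**What to change.** In section 2.6.1, item 2:

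- Name the Kruskal-Wallis test for comparing non-normal variables across the 3 TC groups and the 6 subgroups.
- Keep the Wilcoxon rank-sum test for comparisons that truly involve two groups.
- State that any follow-up comparisons with NTC/-HTN are adjusted, for example by Dunn tests with Holm's method. Other standard procedures would serve as well.

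If the several-sample test was meant all along, the first change only makes that explicit. The cost is about two sentences and no new data. The downside is that adjusted p-values are slightly less favourable. The change should be made before the analysis is run, so that the choice of test does not depend on the results.

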### Morality and communication

2.7

The research of this subject must be approved by the ethics committee of each central research unit before the clinical research begin. The research plan was approved by the Ethics Committee of Tianjin University of TCM (TJUTCM-EC20200005). Informed request for consent was abandoned. It has been registered in the China Clinical Trial Registry with the registration number: ChiCTR2000033863. The patient's personal information will be protected and all data will be collected anonymously. The findings of the study will be published in peer-reviewed journals and disseminated electronically and printed.

## Discussion

3

In China, the death rate of cardiovascular disease still ranks first, accounting for more than 40% of the death rate of residents, and it is much higher than the death rate of tumors and other diseases.^[17]^ According to a report released by the Chinese Expert Consensus on the Comprehensive Management of BP and lipids in hypertensive patients (2019), there are currently about 245 million HTN patients in China. Among the patients with HTN screened by the population, those with at least 1 dyslipidemia accounted for 41.3%, and those with hypercholesterolemia were 9.9%.^[18,19]^

Studies have found that hypercholesterolemia and HTN have both separate and synergistic effects on the occurrence of CHD. The combination of the 2 effects is not a simple superposition effect, but an amplification effect or a product effect. The synergy may be realized through several direct and indirect mechanisms. Endothelial injury theory or oxidized LDL endothelial injury theory may be the initiating mechanism of cholesterol deposition on the arterial wall. Recent studies have found that endothelial cells can maintain hemodynamic stability and affect the process of CHD by producing nitric oxide (NO) and angiotensin-II (AT-II).^[20]^

This study has the following advantages:

(1)The design idea is novel. A study^[13]^ has discussed the effects of diabetes mellitus alone or combined with HTN on CAS. Still, there are few reports focus on the correlation between HTN and hypercholesterolemia and GS of CAS.(2)Standardized diagnostic, inclusion and exclusion criteria. This research protocol sets strict inclusion and exclusion standards and adopts the latest diagnostic standards at home and abroad. For example, compared with the diagnostic standard for HTN in the JNC 7 report,^[21]^ this research uses the latest diagnostic standard for HTN concerning the recently published 2017 ACC/AHA guidelines.(3)The sources of clinical data for this study are extensive. The data of this study comes from multi-centers, and the results are more representative.(4)The design method is accurate. Before performing statistical analysis, we shall invite statistical analysts to make plans and carefully examine the collected clinical data.(5)Strict quality control. Before collecting clinical data, researchers should be trained in a unified way. All CRFs will not take effect until they have been reviewed and signed by researchers in a unified way. Data entry will be done by trained professionals in pairs for the accuracy of the data entry, and the objectivity of the results.

Though we have set strict rules on possible problems of the study program, because of the complexity and variability of the clinical study, some research results may still be affected, and we will further improve the protocol based on actual research. The study will provide guidance for the prevention and treatment of CHD angina pectoris complicated with the disease through clinical research data, and promote its further research.

## Abbreviations

Abbreviations: ACC/AHA = American College of Cardiology and the American Heart Association, BHTC = borderline-high TC, BP = blood pressure, CAG = coronary angiography, CAS = coronary artery stenosis, CHD = coronary heart disease, CRF = case report form, DCF = data clarification form, GS = Gensini score, HTC = high TC, HTN = hypertension, LAD = left anterior descending, LCX = left circumflex, NTC = normal TC, SAP = data verification plan, TC = total cholesterol, TCM = traditional Chinese Medicine.
